### Net-benefit regression-based approach to cost-effectiveness analysis

A second approach to calculating cost-effectiveness will be taken according to net-benefit regression methods to control for imbalances in covariates arising from the non-randomized study design [21],[31],[32]. This method uses patient-level data of economic costs to caregivers and health outcomes, distributing program costs from the last year of the program evenly across children in the endpoint survey. A modification of the net-benefit statistic will serve as the dependent variable, given that outcomes are measured in terms of a health gap measure instead of health expectancy measure [50]. This formulation adds costs to outcomes expressed in monetary terms instead of taking the difference as is done in standard net-benefit calculations. The coefficient on a treatment variable that distinguishes between the starting point and endpoint of the program will be used to represent incremental net benefit. One sided *p*-values from the treatment variable will be used to construct CEACs, using results from a series of regressions that use different values for the ceiling ratio. Due to the non-normality in the distribution of residual values, a generalized linear model using a gamma distribution will be used. Huber-White robust standard errors will be used to address heteroskedasticity, and clustering will be accounted for consistent with study design. Data will be checked for non-linearities to assess whether use of a spline term improves model fit. The importance of influential data points will be checked using DFBETAs, excluding caregivers with the top ten DFBETA scores in sensitivity analysis. Calculations will be performed in Stata 13, using standards for good practice for using statistical regression models in economic evaluations [51].

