**Table 3 Tab3:** **Variables to be tested**

Conceptual framework category	Parameter	Description
Demographic characteristics	Household size	Continuous variable (min = 2 people, max = 23 people in Gujarat and 32 in Uttar Pradesh)
	Child sex	Male =0, female =1
	Child age	Continuous variable (min =2 months, max =59 months)
Characteristics of the social structure	Mother’s education	No or primary education =0, primary education or above =1, secondary education or above =2, tertiary education or above =3
	Father’s education	No or primary education =0, primary education or above =1, secondary education or above =2, tertiary education or above =3
	Scheduled caste	Not a scheduled caste =0, scheduled caste =1
	Scheduled tribe	Not a scheduled tribe =0, scheduled tribe =1
	Other backwards caste	Not another backwards caste =0, other backwards caste =1
Caregiver knowledge	Knowledge about ORS	No knowledge =0, knowledge =1
	Knowledge about zinc	No knowledge =0, knowledge =1
Enabling factors	DAZT program	Initial survey, final survey
	Below poverty line card	No BPL card =0, BPL card =1
	Very poor	Any other wealth quintile =0, second wealth quintile =1
	Poor	Any other wealth quintile =0, third wealth quintile =1
	Less poor	Any other wealth quintile =0, fourth wealth quintile =1
	Least poor	Any other wealth quintile =0, fifth wealth quintile =1
Need factors	Duration of diarrhea	Continuous variable (min = 0 days, max = 15 days in Gujarat and 32 in Uttar Pradesh)
	Blood in the stool	No blood in the stool =0, Blood in the stool =1
Treatment seeking	Seek treatment outside of the home	No treatment sought outside of the home =0, treatment sought =1
Treatment given	Given ORS	No ORS =0, given ORS =1
	Given zinc	No zinc =0, given zinc =1

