### Health outcomes

In the standard cost-effectiveness calculation, health outcomes will be derived from incremental changes in coverage measured in cross-sectional household surveys and inputted into LiST. LiST will estimate the incremental number of lives saved from the study’s start to its completion. The years of life lost (YLL) component of disability-adjusted life years (DALYs) will be calculated using the standard formula from the Global Burden of Disease study [46]. A life expectancy estimate will be taken from WHO life tables representing the midpoint between 1–4 years old. A discount rate of 3% will be used in reference case calculations, and age weighting will not be used to be consistent with the Disease Control Priorities Project second edition (DCP2) [41]. Long-term sequelae such as acute cognitive and psychomotor development effects in young children, the effects of diarrhea on stunting [4], and obesity and related conditions that can occur later in life (cardiovascular disease and diabetes) [47] were not measured and will not be considered. The net-benefit regression approach will be limited to episodes averted as it is impossible to know the specific long-term health outcomes for individual patients. Limitations of drawing data from a single uncontrolled study are recognized [48], although cost-effectiveness analysis is often conducted on data from a single effectiveness study, and conditions in the study sites are not atypical of other relevant settings in low- and middle-income countries.

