Secular trends such as improvements in living conditions, access to safe water, and improved sanitation may have contributed to the decline in diarrhea prevalence in the DAZT study area [60]. However, secular trends may be less relevant for costs as economic growth is unlikely to drive prices for diarrhea treatment down. In addition, this study design is sensitive to sudden changes in the conditions of the study area [61]. The Hawthorne effect is a potential confounder, which would overstate the magnitude of the effect [48]. Regression towards the mean may be problematic [58], which means that if a study had high diarrhea prevalence at beginning, future measurements will be likely to be less extreme. The DAZT study found a 14% prevalence of diarrhea in 2011, while levels were 13% in 2005/6 in Gujarat [36] and were 9% nationwide [7]. Regression to the mean predicts that the prevalence would be lower in future surveys as downward changes would be more frequent than upward changes.

Limitations exist in that household data is based on self-report, reporting bias could have occurred, and long-term outcomes and programmatic outcomes such as quality are not measured. Some researchers argue that only children who receive the recommended 10–14 day course should be included in analysis. However, in the DAZT program, most children only received partial courses of zinc in addition to antibiotics and anti-diarrheal medications. Seasonal effects are possible given that each survey was given at a different point in the monsoon cycle across the years of the study. Limitations of principal components analysis are recognized, such as not evaluating the quality of assets, assuming the first principal component to be an adequate indicator of socioeconomic status, being a relative measure, and producing quintiles with variable arrays of asset ownership [53],[62],[63]. Finally, outcomes will not be evaluated according to severity, which could lead to outcomes such as children with fewer symptoms or shorter episodes having more favorable cost-effectiveness.

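### The regression outcome is a net monetary loss, so with the endpoint coded 1 the programme coefficient is minus the incremental net benefit, not the incremental net benefit as stated

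*Protocol article*

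**What the plan says.** Three statements in the protocol article, under the heading on the net-benefit regression approach, bear on the point.

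- The statistic is modified, "given that outcomes are measured in terms of a health gap measure instead of health expectancy measure". The modification is: "This formulation adds costs to outcomes expressed in monetary terms instead of taking the difference as is done in standard net-benefit calculations".
- The programme effect is read as follows: "The coefficient on a treatment variable that distinguishes between the starting point and endpoint of the program will be used to represent incremental net benefit".
- One-sided p-values feed the acceptability curve (CEAC): "values from the treatment variable will be used to construct CEACs, using results from a series of regressions that use different values for the ceiling" ratio.

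The model is also fixed there: "a generalized linear model using a gamma distribution will be used". The link function is not given. Table 3 lists the programme variable only as "Initial survey, final survey", without 0/1 codes. The Health outcomes section describes the regression outcome differently: "The net-benefit regression approach will be limited to episodes averted". The abstract does the same.

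**The concern.** The dependent variable and the meaning given to its coefficient do not fit together. When the outcome is a harm, adding its money value to cost gives a quantity where more is worse. A programme that lowers both cost and episodes then has a negative coefficient, and one that raises both has a positive coefficient. Calling that coefficient incremental net benefit gives the better programme the worse score.

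The curve built from it is the decision output of this method. The comparison with the Monte Carlo method is one of the study's stated purposes, and the Discussion presents the agreement of the two methods as evidence of robustness. A sign slip could look like disagreement between methods or could reverse the policy reading. The abstract also offers the protocol to researchers planning similar evaluations, who might copy the sentence as it stands.

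**Working it through.** The protocol gives no coefficient, curve value or power figure for this analysis, so there is no stated number to reproduce. The check is algebra, followed by a numerical confirmation.

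**Algebra.** Let C be cost per child, E the episodes experienced (the health-gap reading) and λ the ceiling ratio per episode.

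1. Net benefit with a harmful outcome: NB = −λE − C.
2. The protocol's dependent variable: Y = C + λE = −NB.
3. With endpoint = 1 and start = 0, the coefficient on the difference scale is β = ΔC + λΔE, where Δ is endpoint minus start.
4. Episodes averted per child are −ΔE, so the incremental net benefit is INB = λ(−ΔE) − ΔC = −β.

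This uses no numerical input. Its only assumption about the data is the coding endpoint = 1. That is the ordinary reading: Table 3 lists the initial survey first, its yes/no variables with printed codes use 0 for absent and 1 for present, and programme costs are loaded onto children in the endpoint survey.

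**The model does not restore the sign.** A gamma model needs a positive dependent variable, so Y cannot be negated before fitting. The sign has to be reversed afterwards, and the protocol does not say so.

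**Numerical confirmation.** One simulated data set was used.

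- From the documents: survey sizes 4,200 and 5,080 (Table 2, Gujarat, starting point and endpoint); starting prevalence 14%, from "The DAZT study found a 14% prevalence of diarrhea in 2011".
- Assumed: endpoint prevalence 11%; caregiver cost per episode gamma-distributed with mean 5; programme cost 0.5 per endpoint child; 0.05 added to every cost to keep Y positive; no covariates or clustering; all surveyed children included.

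The simulated data gave ΔC = 0.354 and 0.0374 episodes averted per child, so cost per episode averted was about 0.354 / 0.0374 ≈ 9.5. At λ = 20, INB = 20 × 0.0374 − 0.354 ≈ 0.39. Results with robust standard errors:

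| λ | INB | β (least squares and identity-link gamma) | P(β < 0) | P(β > 0) | β, log-link gamma |
|---|---|---|---|---|---|
| 5 | −0.168 | +0.168 | 0.019 | 0.981 | +0.106 |
| 10 | +0.019 | −0.019 | 0.568 | 0.432 | −0.009 |
| 15 | +0.206 | −0.206 | 0.922 | 0.078 | −0.073 |
| 20 | +0.393 | −0.393 | 0.986 | 0.014 | −0.114 |

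The coefficient is minus the INB in every row. P(β < 0) is the correct curve. P(β > 0), the tail that follows if β is taken to be INB, is its complement (1 − 0.986 = 0.014). With an assumed endpoint prevalence of 17% instead, the coefficient was again minus the INB at every λ tried.

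**Two linked gaps.** With a log link the coefficient is a log ratio (−0.114 at λ = 20, against a money difference of −0.393), so reversing its sign would still not give a net benefit in money. And if the outcome really were episodes averted, a gain, then cost plus λ times that gain would be neither a benefit nor a loss. The algebra above follows the health-gap wording. The section on targeting by subgroup supports it, since it describes a count of treated episodes in which fewer episodes imply episodes averted.

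**The case against.** The strongest reply is that the authors knew the orientation. They call the statistic a modification, give the health-gap reason, cite a source for it and say that it departs from the standard calculation. Authors who took that step may well read the result in the direction proper to a loss. The cited source is not available here, so its sign convention cannot be checked. Tail, coding and plotting convention are also details that an article may leave to a fuller plan. An inverted curve would probably be noticed too: for a costlier programme that averts episodes it would start near 1 at a ceiling ratio of zero and fall as the ceiling ratio rises, opposite to the Monte Carlo curve.

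Much of this stands against a stronger claim. A reader might infer that the planned acceptability curve will be upside down. The document does not support that. Inversion needs both endpoint = 1 and P(β > 0), and neither is written down. The lower tail under the same coding gives the correct curve, as does reversed coding with the upper tail.

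The reply does not remove the mis-signing itself. The missing tail and codes are omissions, but the meaning given to the coefficient is a positive statement, and it conflicts with the statistic defined two sentences before it. It would be true only if the starting survey were coded 1, which nothing in the document suggests.

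**Conclusion.** The stated interpretation has the wrong sign. On the protocol's health-gap wording, cost plus monetised episodes is a net monetary loss. With endpoint = 1 its difference between surveys is minus the incremental net benefit, at every ceiling ratio and for any data.

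The effect on the acceptability curve is conditional. If the one-sided p-value is taken in the direction implied by reading the coefficient as net benefit, each probability becomes its complement, for example 0.019 becomes 0.981 and 0.986 becomes 0.014. If the lower tail is used, the curve is right and only the wording is wrong. The document does not settle which will happen.

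The probabilities are illustrations. Only the survey sizes and the 14% come from the protocol; the costs, the endpoint prevalence and the resulting ceiling-ratio scale are assumptions. The illustration uses the full surveys, although the Conceptual framework section limits the model to children for whom care was sought. None of this affects the sign.

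**What to change.** State the following in the net-benefit regression section:

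1. The dependent variable is net monetary loss, L = cost + λ × episodes experienced. Reconcile this with the abstract and the Health outcomes section, where episodes averted should appear only as the start-minus-endpoint difference.
2. The programme variable is coded start = 0, endpoint = 1; add the codes to Table 3.
3. Incremental net benefit is minus the endpoint-minus-start difference in L, on the money scale. Name the link: with an identity link the difference is the coefficient; with a log link use the marginal (average predicted) difference and its standard error.
4. The acceptability curve plots P(difference < 0) at each ceiling ratio, that is, 1 minus the one-sided p-value against a difference of zero or more.
5. Any worked numerical example is labelled as resting on assumed inputs.

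The cost is a few sentences and one table entry. No data collection or sample size changes. The only extra computation is the marginal difference if a log link is chosen.

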**Table 2 Tab2:** **Sample sizes for each survey**

Survey	Number of participants		Dates
	Gujarat	Uttar Pradesh	
Starting point	4,200	3,889	March 22–May 10, 2011 Gujarat; April 1–June 21, 2011 Uttar Pradesh
Monsoon season			June through beginning of September^a^
Midpoint	1,072	1,790	September 1–October 8, 2012 Gujarat; May 24-October 4 2012 Uttar Pradesh
Endpoint	5,080	1,001	September 28–November 18, 2013 Gujarat; August 25–October 12, 2014 Uttar Pradesh

^a^Although peak diarrhea season lasts until November.

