**Conceptual framework based on Andersen and Newman [**[42]**].**

### Descriptive statistics

Descriptive statistics of the parameters (Table 3) will be calculated according to their means, confidence intervals, and *p*-values reflecting the extent of difference between arms. Comparisons will be made at the start and endpoint of the program. Stata svy commands will be used to account for clustering with *F*-tests used to evaluate the significance of differences between groups. As costs are not normally distributed, significance of differences between components listed in Table 4 at the start and end of the program will be calculated using confidence intervals with bootstrapped standard errors.

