### Strengths and limitations

The main strength of this study is that it provides two different analytic perspectives on cost-effectiveness, allowing assessment of the robustness of results. It’s time frame is comparable to other community-based studies, although the full effect may not be captured as knowledge takes time to fully proliferate, supply systems mature through time, and changes in prescribing patterns can be a gradual process. A heterogeneous mix of patients will be included, enhancing the ability to generalize findings to other areas in India. Recall bias is minimized by asking only about episodes occurring in the last 2 weeks, in keeping with precedent from a previous study [57]. Overall, the quality of the data is high, with interviewers returning to households to fill gaps in missing data.

The main limitation of this study is that the study design of uncontrolled before and after studies is vulnerable to bias, such as secular trends, the Hawthorne effect [48], or regression to the mean [58]. However, the case for clinical effectiveness can be made based on evidence from randomized studies that have found reductions in the prevalence of diarrhea when providers were enabled to give zinc to children with diarrhea [10]. A CHERG review concluded that zinc causes a 23% reduction in diarrhea-specific mortality based on reductions in hospitalization rates, reasoning that this estimate was realistic as it was more conservative than reductions in all-cause or diarrhea-specific mortality found in other studies [14]. This evidence is consistent with the 2004 WHO/UNICEF endorsement of zinc for treating child diarrhea, which concluded that zinc reduces the severity and duration of acute diarrhea, and the number of episodes in the 2–3 months after treatment [8]. Since equipoise existed for the DAZT delivery strategy, but not for the effectiveness of zinc, the before and after study design was deemed to be the appropriate form of evaluation [59]. The intervention has since been rolled out statewide in Gujarat, and the final survey is underway in Uttar Pradesh.

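### Deleting the ten top-DFBETA caregivers trims the small Uttar Pradesh endpoint survey far more than the start survey, so this sensitivity analysis leans toward the programme even when nothing changed

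*Protocol article*

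**What the plan says.** The section on the net-benefit regression describes a gamma generalized linear model with robust standard errors and allowance for clustering. The dependent variable is a modified net benefit: "This formulation adds costs to outcomes expressed in monetary terms instead of taking the difference". Because the outcome is a health gap, a lower value is better. The effect of interest is defined as follows: "The coefficient on a treatment variable that distinguishes between the starting point and endpoint of the program will be used to represent incremental net benefit". One-sided p-values for this coefficient feed the acceptability curves.

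Influential points are to be checked with DFBETAs, "excluding caregivers with the top ten DFBETA scores in sensitivity analysis". The number ten is fixed. The text does not say whether scores are ranked by absolute value or with sign, and nothing balances the deletions between the two surveys.

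Table 2 gives the survey sizes, Gujarat first and Uttar Pradesh second: "Starting point 4,200 3,889" and "Endpoint 5,080 1,001". The section on descriptive statistics concedes the skewness: "As costs are not normally distributed". Under strengths and limitations, assessing robustness is presented as the study's main strength: "The main strength of this study is that it provides two different analytic perspectives on cost-effectiveness, allowing assessment of the robustness of results".

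**The concern.** A check for influential records should show whether the conclusion hangs on a handful of observations. For a coefficient that contrasts two surveys, however, influence depends on survey size as well as on how unusual the record is. Where one survey is much smaller, the list of top DFBETAs is largely a list of that survey's extreme values.

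With right-skewed costs those extremes are expensive episodes, which are part of the mean cost that a cost-effectiveness analysis must estimate. Removing them lowers the mean of the smaller survey and leaves the other almost as it was. The refit then compares a top-trimmed survey with a nearly untrimmed one, and the expected difference is not zero when the programme did nothing. In Uttar Pradesh the smaller survey is the endpoint, so the shift is toward the programme. A reader could take that shift as evidence about cost-effectiveness when it comes from the deletion rule.

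**Working it through.** The article gives no figure for this check, so there is none to reproduce.

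**Inputs from the article.** Uttar Pradesh n0 = 3,889, n1 = 1,001; Gujarat n0 = 4,200, n1 = 5,080 (Table 2). Ten deletions; lower outcome is better; gamma model with robust errors (net-benefit section). Diarrhoea prevalence 14% in 2011 (strengths and limitations).

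**Assumed, because not given.** Cost spread, cluster size, link function, and a one-sided 5% level used only as a yardstick.

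**Step 1: influence by survey.** For a two-group coefficient, the DFBETA of record i in group g is about (y_i − m_g)/n_g, divided further by m_g under a log link. At equal means, equal residuals have influence in the ratio n0/n1:
- Uttar Pradesh: 3,889/1,001 = 3.9 in favour of endpoint records, although the endpoint is only 1,001/4,890 = 20% of the sample.
- Gujarat: 5,080/4,200 = 1.2 in favour of start records.

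**Step 2: effect of deletion.** Removing k records from the endpoint changes its mean by −Σ(y_i − m1)/(n1 − k). If the removed values lie above the mean, this is negative, which is toward the programme.

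**Step 3: simulation with identical distributions in both surveys.** The ten largest absolute DFBETAs are deleted, the coefficient is refitted, and support for the programme is counted at z < −1.645. Lognormal log-SDs of 1 and 1.5 correspond to CVs of √(e^1 − 1) = 1.3 and √(e^2.25 − 1) = 2.9. Clustered settings use clusters of 20 and both log and identity links.

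| Uttar Pradesh setting, no true change | Deletions from endpoint | Support before | Support after |
|---|---|---|---|
| 3,889/1,001, independent, CV 1 to 3 | 80-97% | 5-8% | 55-73% |
| Gamma GLM with covariates (60 runs) | 94% | 7% | 58% |
| Clustered, cost only, log-SD 1 or 1.5 | 79-92% | 6-10% | 42-64% |
| Clustered, 14% with an episode, ceiling ratio 0 | 88% | 7-9% | 71-77% |
| Same, ceiling ratio equal to mean episode cost (5/5) | 93-94% | 4-5% | 53-56% |
| Same, 10 times mean episode cost (50/5) | 100% | 5-7% | 23-24% |
| Same, 114 times mean episode cost (570/5) | 100% | 6% | 17-19% |
| Clustered, programme cost exactly offset by lower endpoint costs | 79-80% | 6% | 26-28% |
| Episodes only, 14% of each survey (544/140) | 63-97% | 6-12% | 71-82% |
| Episodes only, unequal prevalence (400/200 or 311/200) | 54-63% at 311/200 | not tabulated | 25-42% |

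At the highest ceiling ratio the deleted records are endpoint children with an episode, not those with high cost as such. The direction is the same.

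**Step 4: controls.** Two equal surveys of 2,445 (4,890/2) give 50% endpoint deletions, a shift near zero and 6-8% support after deletion. Dropping the same share of the largest values from each Uttar Pradesh survey gives 5-12%, the same as with no deletion. The cause is therefore the unequal trimming, not trimming itself.

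**Step 5: ranking with sign.** Uttar Pradesh at 3,889/1,001: all deletions come from the endpoint, and support after deletion is 43-89%.

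**Step 6: Gujarat.** Absolute ranking shifts the estimate by about 0.2 to 0.3 standard errors against the programme, and rejection against it is about 8-14% in the unclustered runs. Signed ranking reverses this, with 14-49% support for the programme.

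**The case against.** The strongest reply is that this is a secondary diagnostic. The full-data regression remains the reference result, the Monte Carlo analysis beside it makes no such deletion, and an influence deletion is supposed to move the coefficient. The article sets no significance level and no accept/reject rule; p-values only build acceptability curves. All of this stands, and it limits the consequence to how the robustness check is read. A reader might infer that the main Uttar Pradesh conclusion is biased, or that a null result will be reported as favourable. The article supports neither.

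The second reply concerns size, and it also stands. No cost spread is given. The section on the conceptual framework limits the model to children who sought care, so Table 2 is not the regression sample and its 3.9 ratio may not carry over. The Uttar Pradesh surveys fell in different seasons (April-June and August-October), so equal prevalence cannot be assumed. The 1,001 may not be final: Table 2 sizes are described as achieved, yet the limitations section says the last Uttar Pradesh survey is still in the field. No single rejection rate should be quoted.

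Third, a reader might infer that the rule necessarily pushes the two states in opposite directions and so creates a difference between them. That holds only under absolute ranking, and the Gujarat shift is then small. Under signed ranking, which the wording leaves open, both states move toward the programme.

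The objection that such detail belongs in a fuller analysis plan carries less weight. The article does not leave the rule open; it fixes the number and the criterion, and the asymmetry follows from them.

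**Conclusion.** The point holds for the direction in Uttar Pradesh. In every setting tried there (both rankings, both links, with and without clustering), the top-ten deletion removed mainly endpoint records and moved the refit toward the programme when nothing had changed. With absolute ranking, one-sided 5% support rises from about 5-10% to roughly 17-80%. The lower end comes from clustered data with a very high ceiling ratio, the upper end from an episode-level sample with equal prevalence. Where the true figure lies depends on skewness, clustering, ceiling ratio and the real regression sample.

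For Gujarat the size and direction depend on the ranking, and the article should state it. The main estimate is untouched. What fails is the use of this refit as evidence of robustness, which matters because the article rests its main strength on robustness. The change is worth making but does not threaten the primary analysis.

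**What to change.** 1. State that DFBETAs are for the start/endpoint coefficient and ranked by absolute value. Use them to flag records for verification, and report how many flagged records come from each survey.
2. Base the robustness refit on a rule that treats both surveys alike: cap household cost in both at one common percentile of the pooled data within each state (for example the 99th), or drop the same proportion of the largest values from each survey. Show it beside the full-data result, which stays the reference.
3. If the top-ten deletion is kept, label it an influence diagnostic and do not read it as evidence for or against cost-effectiveness.

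The cost is a few sentences of plan wording and one changed refit, with no new data. Capping or trimming slightly understates mean cost in both surveys, which is why it should remain a sensitivity analysis.
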